#### Primary Analysis

The primary objective of this study is to determine the overall and procedure-specific incidence of *S. aureus* SSI in Europe. The primary analysis will consist of calculating the incidence using 95% CIs.

#### Secondary Analysis

The secondary analysis will consist of determining the overall and procedure-specific outcomes of *S. aureus* surgical site infections in Europe as well as the overall and procedure-specific economic burden of *S. aureus* SSI in Europe. Therefore, patients having established *S. aureus* SSI will be matched 1:1 to controls from the same center based on a propensity score and optimal matching with the following covariates: (1) type of procedure, (2) age, (3) ASA score, (4) BMI, (5) duration of procedure (as percentile for this procedure), (6) diabetes, and (7) sex.

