### Rationale

Active, prospective SSI surveillance lowers SSI rates [13]; therefore, unbiased SSI rates should be determined by retrospective, non-interventional studies. This cohort study will sample a large percentage of the surgical population and thereby generate representative data. For the selection process and documentation of the overall cohort, we will limit data items to those that are generally available in electronic form, thus facilitating the sampling of an adequately sized and complete cohort with comparably low effort. Feasibility analysis of candidate study centers will assess center capability for electronic data provision. If needed, single data items may be waivered during the selection process. In this case, these data items would instead be documented as part of the nested case-control study.

The nested case-control part of this study is necessary to generate data required for outcomes and cost analyses, as most centers will not have electronic records sufficiently detailed to allow this analysis for the whole cohort. The approach avoids bias that has been introduced, for example by relying on reimbursement data to estimate costs [14], and thus describing the SSI price rather than its cost. Therefore, the best possible approach to an accurate, precise cost analysis is manual documentation by on-site medical personnel (eg, study nurses). Documentation must comprise relevant cost drivers of SSI cases and well-matched controls to allow analyses of incremental costs caused by SSI. On-site medical personnel would receive appropriate electronic case report form (eCRF) training prior to commencing documentation. In addition, manual data capturing allows concomitant plausibility checking.

Nesting the case-control study within a cohort ensures generalizability of the case-control results to the respective center as well as the cohort and, by means of a representative cohort, to the overall surgical population in Europe.

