##### Detection of
*S. aureus* Surgical Site Infection

As a first step, we will export the data listed in the Data Collection Cohort section from all patients who underwent surgery in each center in 2016. We expect a minimum of 100,000 cases to be included in the cohort. *S. aureus* SSI that occurred in 2016 will be detected using microbiological data. 

To ensure feasibility, only centers with the capability of electronic microbiologic data export will participate. All patients presenting a *S. aureus* infection from the following will be identified: (1) wound swabs, (2) aspirates, (3) samples obtained during surgery, and (4) blood cultures.

Subsequently, electronic matching with clinical data will be performed in order to determine those patients who underwent a surgical procedure and had an *S. aureus* infection. This approach provides a sensitivity of 100% for identification of proven *S. aureus* SSI cases.

Data collected for surgical site infection cases.Length of hospitalizationLength of intensive care unit (ICU) stayReason for ICU stay; attribution to surgical site infections (SSI)Hours of mechanical ventilationHemodialysisSurvival at 30 and 90 daysIn case of death, attribution to SSINecessity for revision surgeryIn case of SSI, attribution to SSINecessity for readmissionIn case of readmission:ReasonAttribution to SSILength of hospitalizationLength of ICU stayHours of mechanical ventilationAll antibiotic treatments, including duration and dosageAll antibiotic treatments, including durationFunctional status at admission and at final dischargeCausative pathogens including resistance patternsType of SSI according to European Centre for Disease Prevention and Control criteria

All patients identified will be documented manually. Occurrences of SSI will be verified on a case-by-case following the criteria of the Hospital Acquired (HAI) SSI protocol [1].

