### Limitations

A limitation of this study is the inability to detect late infections occurring post discharge by only analyzing in-patient laboratory data for SSI case identification. Depending on the procedure in question, infections occurring after discharge constitute a notable percentage of SSI. A post discharge surveillance approach will be subject of a future sub study.

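### Cases are found only from in-patient laboratory data, so per-case outcomes and costs describe S. aureus SSI diagnosed in hospital, yet the plan reads them as S. aureus SSI in general

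*Protocol article*

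**What the plan says.** - **Case source.** Discussion, Limitations, concedes an "inability to detect late infections occurring post discharge by only analyzing in-patient laboratory data for SSI case identification". It adds that, depending on the procedure, "infections occurring after discharge constitute a notable percentage of SSI", and defers the matter: "A post discharge surveillance approach will be subject of a future sub study". The section on detecting S. aureus SSI nevertheless states: "This approach provides a sensitivity of 100% for identification of proven *S. aureus* SSI cases".
- **Controls.** Under Controls, a control needs the same procedure and no SSI. Under Secondary Analysis, cases "will be matched 1:1 to controls from the same center based on a propensity score and optimal matching with the following covariates": procedure, age, ASA score, BMI, duration of procedure, diabetes and sex. None concerns discharge, readmission or time of diagnosis.
- **Outcomes and costs.** Textboxes 1 and 3 record length of hospitalization, ICU stay and readmission, with attribution to SSI. The four cost drivers under Exploratory Analysis are all in-hospital resources: hospital days, ICU days, ventilation hours and revision surgery. Principal Findings attributes 90% of excess SSI cost to length of stay.
- **Target.** The Secondary Objectives concern outcomes and economic burden of S. aureus SSI in Europe, without restriction to SSI diagnosed in hospital. Rationale wants "well-matched controls to allow analyses of incremental costs caused by SSI". Both Rationale and Principal Findings say that nesting makes the results generalizable to the overall surgical population in Europe.

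**The concern.** For an infection that starts after discharge, entry into the case group appears to require a further in-patient stay. That stay is also a recorded outcome and the main cost driver. Infections managed wholly outside hospital cannot enter. Matching on baseline and procedural covariates cannot remove this, because the selection acts on what happens after the procedure and only among cases.

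The Limitations section treats the gap purely as missed detection, which bears on the primary objective (incidence). It does not say that the secondary comparison then rests on cases selected for needing in-patient care. At stake is the reading of every per-case result: readmission share, added hospital days and added cost would be taken as those of the average S. aureus SSI when they belong to the hospital-diagnosed subset.

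**Working it through.** **The plan's own figure.** Sample Size and Statistical Analysis assume 1.5% of 150,000 patients: 0.015 × 150,000 = 2250 cases, matched to 2250 controls. This reproduces exactly. The question is which SSIs those cases represent.

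**Set-up.** Split all true S. aureus SSIs into a (found in the index stay), b (post-discharge, in-patient again) and m (post-discharge, never an in-patient), with a + b + m = 1. Let p be the share arising after discharge and r the share of those who return as in-patients. Then b = p·r, m = p(1 − r) and a = 1 − p. Let c be the excess in-hospital cost of a missed case relative to a detected one. The article gives none of p, r or c; all values below are assumptions. Background readmissions unrelated to SSI are ignored.

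**Formulas.**
- Readmission share: true b; among detected cases b/(a + b) = b/(1 − m). Ratio: 1/(1 − m).
- Excess in-hospital cost per case, detected relative to all: 1/(1 − m + c·m).

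**One worked case.** With p = 0.4 and r = 0.5, b = 0.20, m = 0.20 and a = 0.60.
- Readmission share: 0.20/0.80 = 25% observed against 20% true.
- Cost factor: 1/0.80 = 1.25 at c = 0; 1/(0.80 + 0.10) = 1.11 at c = 0.5; 1 at c = 1.

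**Range.** With p from 0.2 to 0.6 and r from 0.25 to 0.75, m runs from 0.2 × 0.25 = 0.05 to 0.6 × 0.75 = 0.45.

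| | m = 0.05 | m = 0.45 |
|---|---|---|
| Readmission ratio, 1/(1 − m) | 1.05 | 1.82 |
| Cost factor, c = 0 | 1.05 | 1.82 |
| Cost factor, c = 0.5 | 1.03 | 1.29 |
| Cost factor, c = 1 | 1.00 | 1.00 |

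**Could missed SSIs among the controls offset this?** Taking 1.5% as the true incidence and m = 0.45, they make up 0.015 × 0.45 / (1 − 0.015 + 0.015 × 0.45) = 0.68% of the control pool, which is too few.

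**Total in-hospital burden.** Let I be the true incidence and D the excess cost per detected case. The observed total is I(1 − m) × D. The true total is I × D(1 − m + c·m). At c = 0 the two are equal. At m = 0.20 and c = 0.5 the observed total is 0.80/0.90 = 0.89 of the true one, so it is understated.

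**The case against.** - **Literal reading of the limitation.** The Limitations sentence can be read to mean that no late post-discharge infection is detected at all. Readmission is then not a route into the case group, and the readmission-share formula does not apply. This is a fair point: entry only through a further in-patient stay is an inference. The recording of readmission and its attribution to SSI, and the 90-day window for SSI under Data Collection, make it the more natural reading. On the literal reading the per-case results still describe only patients who were in hospital at diagnosis.
- **Inflated burden.** A reader might infer that the planned economic burden is overstated. The article does not support that. If missed cases use no hospital resources, lower incidence and higher per-case cost cancel. Exploratory Analysis multiplies unit price by units used, and nowhere applies a per-case cost to a wider incidence.
- **Short-stay procedures.** A reader might also suppose that these are worst affected. The article says only that the post-discharge share depends on the procedure.
- **Direction.** Patients readmitted to another hospital are missed and may be costly, which pulls the other way. The upward direction is therefore probable, not certain.
- **Controls.** Not conditioning controls on readmission is correct, since it is an outcome. The fault lies in case ascertainment set against an unrestricted target, not in the covariate list.
- **Already disclosed, or left to the analysis plan.** Missed detection is disclosed, and costs are to be stratified by depth of SSI. Neither separates index-stay from readmission diagnoses. The article itself fixes the case source, the control definition and the generalizability claim, and these do not fit together.

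**Conclusion.** The point stands for per-case results. As planned, readmission, length of stay and in-hospital cost per case are those of S. aureus SSI diagnosed in hospital. They probably overstate the average over all S. aureus SSI if missed cases use fewer hospital resources, which is plausible because every listed cost driver is an in-hospital resource. The size cannot be derived from the article; the factors shown illustrate assumed shares and costs and are not estimates for this study.

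The claim of 100% sensitivity for proven cases does not answer the point, since it cannot cover infections that never yield an in-patient sample.

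**What to change.** 1. In Secondary Analysis, define the outcome and cost estimand as S. aureus SSI diagnosed in hospital.
2. Report case-control differences separately for SSI diagnosed during the index stay and SSI diagnosed at readmission. The date of diagnosis is already listed under Data Collection, Cohort; the recorded length of hospitalization and readmission data should allow it to be placed before or after index discharge.
3. Do not compare the occurrence of readmission with controls in the second group, where it is 100% by construction.
4. Extend the limitation in the Discussion from missed detection to per-case outcomes and costs.
5. Qualify the generalizability statements in Rationale and Principal Findings accordingly.

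The cost is wording and one stratification, with no new patients. The price is smaller strata, mainly for rare procedures, and a narrower claim.

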#### Exploratory Analysis

Based on case-control matching, the composition of the surgical patient population in Europe will be characterized and the number of patients at risk for *S. aureus* SSI estimated.

The economic burden, including direct treatment and indirect costs, imposed by *S. aureus* SSI in Europe will be calculated by multiplication of the per-unit price for major cost drivers with the number of units used. The following variables will be included in the cost analysis as major cost drivers: (1) length of hospitalization, (2) length of ICU stay, (3) hours of mechanical ventilation, and (4) number and type of revision surgeries.

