## Methods

### Study Design

This is a retrospective, multinational, multicenter cohort study with a nested case-control. The study includes all surgical procedures at a participating center in order to prevent selection bias and strengthen the understanding of SSI risk by determining incidence for all common surgical procedures. Furthermore, the study will analyze the risk composition of the surgical patient population to enable the calculation of the number of patients at risk in the overall surgical population in Europe.

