### Study Procedure

#### Populations

Data will be assessed in the cohort and the nested case-control population (Textbox 1).

The following are the matching criteria for the nested case-control population: (1) type of procedure, (2) age, (3) BMI, (4) duration of procedure (as a percentile for this procedure), (5) diabetes, and (6) sex.

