#### Sample Size

We assume a 1.5% incidence rate of *S. aureus* SSI. Incidence rates can be determined with a 95% CI of plus or minus 0.5% by observing 1500 surgical procedures, assuming a mean *S. aureus* SSI rate of 1%. Lower incidence rates would result in smaller 95% CIs with a similar sample size or similar CIs with a smaller sample size. Therefore, at least 15 centers should be included in the analysis, resulting in 90,000 to 150,000 patients observed patients. This will allow us to calculate incidence rates with meaningful precision for all surgical procedures performed on at least 1% to 1.5% of respective patients. To further broaden the scope of this study, 1 or 2 centers per country will be included specializing in types of surgery not traditionally performed at academic surgical centers but highly relevant to the prevention of SSI in otherwise healthy patients (eg, plastic surgery). Assuming a 1.5% incidence rate of *S. aureus* SSI, in a population of 150,000, 2250 cases will be matched to 2250 controls.

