##### Controls

Cases will be matched to controls that received the same procedure but did not develop a SSI. Further variables to be included are (1) age; (2) sex; (3) American Society of Anesthesiologists (ASA) score; (4) BMI; (5) duration of operation (as a percentile); and (6) diabetes. If available, comorbidities other than diabetes and underweight or overweight as well as the Charlson comorbidity index [15] and its components will be included.

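### The make-up of the surgical population and the number at risk are assigned to the case-control match, a sample selected on infection; the full cohort is the right basis

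*Protocol article*

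**What the plan says.** Exploratory objectives 1 and 2 are to describe the make-up of the European surgical population and to estimate how many patients are at risk of *S. aureus* SSI. The only analysis statement that assigns a data basis to them is the opening sentence of Exploratory Analysis: "Based on case-control matching, the composition of the surgical patient population in Europe will be characterized". The number at risk follows in the same sentence and on the same basis.

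The matched sample is defined elsewhere in the article:

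- Secondary Analysis: cases "will be matched 1:1 to controls from the same center based on a propensity score and optimal matching". The covariates are procedure type, age, ASA score, BMI, duration percentile, diabetes and sex.
- Controls: "Cases will be matched to controls that received the same procedure but did not develop a SSI".
- Sample Size: "in a population of 150,000, 2250 cases will be matched to 2250 controls".

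Other sections point to a different basis:

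- Study Design gives this aim: "analyze the risk composition of the surgical patient population to enable the calculation of the number of patients at risk". The sentence refers to European surgical patients as a whole and does not mention the matched subset. Principal Findings repeats this.
- Nested Case-Control Design gives the nested part one purpose, the analysis of costs and outcomes.
- Textbox 1 and the Cohort list under Data Collection have demographics, procedure, duration, BMI, comorbidity codes and wound class exported for the whole cohort. The Cohort list says that its variables serve description only.

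**The concern.** A case-control sample is selected on the outcome. Here half of it is infected by construction, and the other half is picked to look like the infected half. Neither half represents surgical patients in general. Because the 1:1 ratio is fixed by the investigators, the proportion infected in the sample says nothing about the proportion infected in the population.

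If the sentence is carried out as written, factors that raise the risk of *S. aureus* SSI will look more common among surgical patients than they are, and factors that lower it will look rarer. The number at risk has no valid starting point in this sample. The article's Conclusions say that the findings may help in designing vaccine trials. Population make-up and number at risk are natural inputs to such work, although the article does not link them to trial sizing.

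**Working it through.** **1. Reproduce the plan's own figure.** Inputs from Sample Size: 150,000 patients, 1.5% incidence, 1:1 matching.

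- Cases = 150,000 × 0.015 = 2250, with 2250 controls. This agrees with the plan.
- Matched sample = 4500, which is 4500 / 150,000 = 3% of the cohort.

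**2. Over-representation of infected patients.** The case share is 2250 / 4500 = 50% in the matched sample.

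- At 1.5% incidence: 50 / 1.5 = 33.3-fold.
- At the 1% that Sample Size also assumes: 50 / 1 = 50-fold.

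**3. Effect on the make-up of the sample.** Let *f* be the share of the cohort with a matching factor and RR the risk ratio for *S. aureus* SSI with the factor against without it. The share among cases is

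*f* × RR / (*f* × RR + 1 − *f*).

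Controls matched exactly on the factor have the same share, and so has the whole matched sample. The article gives neither *f* nor RR, so the values below are assumptions, shown as a range.

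| Cohort share *f* | RR 1 | RR 1.5 | RR 2 | RR 3 |
|---|---|---|---|---|
| 5% | 5% | 7.3% | 9.5% | 13.6% |
| 10% | 10% | 14.3% | 18.2% | 25.0% |
| 20% | 20% | 27.3% | 33.3% | 42.9% |

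Example: *f* = 0.10, RR = 2 gives 0.20 / (0.20 + 0.90) = 18.2%. The group without the factor shrinks correspondingly, from 90% to 81.8%.

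**4. Procedure mix.** The share in the matched sample is the cohort share × procedure rate / overall rate. With an assumed procedure at 10% of operations and an overall rate of 1.5%:

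- procedure rate 3%: 10% × 3 / 1.5 = 20%;
- procedure rate 0.5%: 10% × 0.5 / 1.5 = 3.3%.

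**5. Simple re-weighting does not repair it.** Weighting cases and controls back to 1.5% and 98.5% in the RR 2 example gives 0.015 × 18.2% + 0.985 × 18.2% = 18.2%, because exactly matched controls carry the cases' distribution. Recovering the cohort mix would need an inclusion probability for each control. The article describes none, and none is needed when the cohort itself is available.

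**The case against.** **The sentence may be loose wording.** Most of the article points to the cohort: the stated purpose of the nested part, the cohort-wide export and Study Design. This is a fair account of how the sentence may have arisen. It remains the only analysis statement for these two objectives, and Rationale and Principal Findings say that nesting ensures generalizability, so an analyst could follow it literally.

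**The phrase might refer to the propensity model.** Principal Findings describes a propensity score from logistic regression, and fitting one would need data beyond the matched pairs. Nothing in the text says that this score will be used to describe the population or to count those at risk, so this reading is not supported.

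**The distortion may be small.** Background says that available data suggest similar *S. aureus* SSI rates across procedures and that the study hopes to show independence from procedure. If so, the procedure mix would be undistorted (the RR 1 column). Any other matching factor related to risk would still be distorted. Propensity matching is also only approximate for single factors, so the exact-match figures are a limiting case. Both qualifications stand.

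**The cohort may not hold every item.** Rationale allows single items to be waived from the cohort export and recorded only in the nested part, and the Cohort list omits ASA score although Textbox 1 includes it. This stands and is dealt with in the fix.

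**A reader might infer that the at-risk count would be inflated by the ratios in the table,** for example 18.2 / 10 = 1.82. The article does not support that. These ratios apply to one factor's share under assumed risk ratios, the number at risk is not defined as carriers of one factor, and low-risk groups shrink at the same time.

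**Conclusion.** The point holds: as written, the data basis named for two exploratory objectives is wrong and contradicts other sections of the article. That the matched sample is selected on the outcome, and that it carries no information on absolute risk, follows from the 1:1 design and needs no assumed figure. The size of the distortion in population make-up does need one. It runs from none at a risk ratio of 1 to 10% appearing as 25.0% at a risk ratio of 3, given exact matching. The direction and size of the net effect on the at-risk count cannot be determined from the article.

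Severity is moderate. It would be tempting to conclude that the study's incidence results are compromised. They are not: Primary Analysis calculates incidence without reference to the matched pairs, and the secondary outcome and cost analyses are the proper use of the matched sample.

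**What to change.** In Exploratory Analysis, replace the opening phrase that names the matching with *Based on the full cohort*. Then state that:

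- the make-up of the surgical population is described from all cohort patients;
- the number at risk is estimated from cohort incidence by stratum (procedure and risk group) together with the size of each stratum;
- the matched sample is used for outcomes and costs only;
- for any item waived from the cohort export at a center, population make-up is reported only from centers that hold the item cohort-wide, and those centers are named as the basis.

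The cost is a rewritten sentence and a short rule for waived items. No new data collection is needed, since the cohort export is already planned. The one price is that waived items will be described on fewer centers.

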With SSI rates being the primary endpoint, SSI detection methodology is crucial in this study. Prior studies and surveillance effort, if specifying detection methodology at all, are usually limited to the analysis of administrative code data [14,15]. However, a recent publication demonstrated that using bacteriological data is superior and combining both—administrative and bacteriological data—could be even more advantageous [16]. In this very study, the detection by means of bacteriologic data will result in high sensitivity, specificity, and negative predictive values (96.4%, 91.4%, and 99.9%, respectively) for deep SSI with no significant difference to the use of both types of data.

Cases are matched 1:1 to controls within each center by software provided by the coordinating center. Matching cases and controls within centers addresses the need for risk-adjustment to institutional characteristics and practices. Cases are matched to controls that received the same type of procedure. Individual pair-wise matching will be used, utilizing optimal matching to ensure the overall smallest possible Euclidean distance between cases and controls. Acknowledging the limited utility of using the National Healthcare Safety Network (NHSN) risk index, which only accounts for the existence of certain risk factors but not their composition, a propensity score is determined by logistic regression.

Costs are calculated by multiplication of the per-unit price for major cost drivers with the number of units used. Minor cost drivers, such as drug use, will be disregarded, as length of stay has been repeatedly shown to account for 90% of excess SSI costs [11].

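### Length of hospitalization is priced with no restriction to days after the operation, and no matching list contains pre-operative stay, so any remaining pre-operative difference enters the SSI excess

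*Protocol article*

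**What the plan says.** **Aim.** The Rationale section justifies the nested case-control part by the need for "well-matched controls to allow analyses of incremental costs caused by SSI". The target is thus a causal increment, not a description of total stay.

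**What is collected and priced.** Textbox 1 (nested case-control data) and Textbox 3 (SSI case data) list the length of the hospital stay, with no start point and no split at the operation. The Exploratory Analysis section puts "length of hospitalization" first among its drivers, which it names as "1) length of hospitalization, (2) length of ICU stay, (3) hours of mechanical ventilation, and (4) number and type of revision surgeries", and costs them by "multiplication of the per-unit price for major cost drivers with the number of units used". The Discussion (Principal Findings) adds that "length of stay has been repeatedly shown to account for 90% of excess SSI costs".

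**Eligibility.** Textbox 2 excludes patients who already have an SSI when they are operated on.

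**Matching.** The Populations section lists "1) type of procedure, (2) age, (3) BMI, (4) duration of procedure (as a percentile for this procedure), (5) diabetes, and (6) sex". The Secondary Analysis section lists "1) type of procedure, (2) age, (3) ASA score, (4) BMI, (5) duration of procedure (as percentile for this procedure), (6) diabetes, and (7) sex" for the propensity score. The Controls section requires the same procedure and adds age, sex, ASA score, BMI, operation duration and diabetes, with comorbidities and the Charlson index if available. Matching is within center.

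**Regression.** The Statistical Analysis section plans a multivariable regression of overall cost on SSI occurrence and names no covariates.

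**The concern.** An SSI can lengthen only the part of the stay that follows the operation. Given the exclusion in Textbox 2, the days from admission to the index operation precede every SSI the study counts. If they are included in the priced unit, they cancel between cases and controls only when their means are equal after matching.

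The matching lists do not secure that equality. The duration variable in them is operating time, not time in hospital. Matching on procedure does not separate a patient admitted for planned surgery from one who was already an inpatient or came as an emergency.

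The secondary objectives on economic burden and the excess-stay outcome are at stake. Because length of stay carries 90% of excess cost by the article's own figure, an error in excess stay passes almost entirely into excess cost.

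**Working it through.** **1. The plan's own figure.** The number of pairs is 0.015 × 150,000 = 2250, which reproduces the 2250 cases and 2250 controls in the Sample Size section. The article states no length-of-stay figures, so there is nothing further to reproduce.

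**2. Side by side.**
- Quantity wanted: cost caused by SSI (Rationale).
- Quantity priced: hospital days, unrestricted (Exploratory Analysis).
- Days that cannot be caused by SSI: all those before the operation (Textbox 2 exclusion).
- Variables that would balance those days: absent from all three matching lists. Admission date, operation date and pre-operative days are also absent from the listed data items (Textboxes 1 and 3; Data Collection, Cohort).

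**3. Decomposition.** Stay counted from admission is pre-operative plus post-operative days. Let T be the true post-operative excess and D the mean case-minus-control difference in pre-operative days left after matching. Setting other sources of bias aside,

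estimated excess = T + D, and relative error = D / T.

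**4. Numbers.** T and D are assumptions, because the documents give neither. Overstatement of excess stay:

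| D (days) | T = 5 | T = 10 | T = 15 |
|---|---|---|---|
| 0 | 0% | 0% | 0% |
| 0.5 | 10% | 5% | 3.3% |
| 1 | 20% | 10% | 6.7% |
| 2 | 40% | 20% | 13.3% |
| 3 | 60% | 30% | 20% |

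A negative D would understate the excess by the same fractions.

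**5. Carry-over to cost.** If length of stay makes up 90% of true excess cost and the other drivers are unaffected, the cost error is 0.9 × D / T. At T = 10 and D = 1, 2 or 3 this is 9%, 18% or 27%.

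**6. Against random error.** With 2250 pairs, the 95% half-width for the mean excess stay is 1.96 × SD / √2250. For an assumed SD of the paired difference of 10, 20 or 30 days this is 0.41, 0.83 or 1.24 days. A 1-day shift would exceed the first two and fall just short of the third; 2 or 3 days would exceed all three. A larger sample does not shrink the shift.

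**The case against.** **The start of the stay is not stated.** A reader might infer that the plan defines the measure as the whole admission. The documents do not say so: they give a label with no counting rule, and a condensed article may leave the rule to the full protocol, the eCRF or the SAP. This stands as a limit on the wording. It does not dispose of the point, because the cost drivers and matching covariates are stated explicitly and, followed as written, leave pre-operative imbalance in the comparison.

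**It is not the main outcome.** A reader might also take length of stay to be the study's main outcome. That is unsupported. Survival, ICU stay, revision, readmission and functional status are listed beside it, and none is ranked first. Only its weight in cost is documented.

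**Bias needs an imbalance.** Same-center, same-procedure matching may absorb much of the difference, helped by the ASA score in two of the three lists and by comorbidities where available. That is correct, and nothing in the documents shows that cases wait longer before surgery. The planned regression cannot settle the matter either way: with no covariates named, it can neither be credited with adjusting for pre-operative stay nor be said to omit it.

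**Attribution to SSI.** Textbox 3 ties attribution to the ICU stay and shows none for the index hospital stay. In Textbox 1 the layout is lost, and the attribution item could cover both stays. The contrast is therefore suggestive, not decisive.

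**Conclusion.** The point holds in conditional form. The dominant cost driver is listed and priced without restriction to post-operative days, in plain reading it runs from admission, and no matching list contains pre-operative stay or urgency. Any pre-operative difference left after matching would be attributed to SSI in both excess stay and excess cost.

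It would go too far to conclude that the reported excess will be overstated. The documents give neither the direction nor the size of an imbalance. The range of 0% to 30% rests on an assumed true excess of 10 days and an assumed imbalance of 0 to 3 days. At zero imbalance there is no bias, only added variance.

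The consequence is confined to the cost and length-of-stay comparisons. The incidence estimates do not depend on this item.

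**What to change.** For the incremental stay and cost comparison, count index-admission hospital days, ICU days and ventilation hours from the date of the index operation, in cases and controls alike. Record pre-operative days as a separate variable and include it as a covariate in the cost regression planned in the Statistical Analysis section. Total stay can still be reported descriptively.

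The cost is one derived or added data field and a sentence of definition. Admission and operation dates are not among the listed items, so their availability should be confirmed with the centers. This should be done before the database closes (planned for September 2018): data are held anonymously without pseudonyms, so a total stay captured alone may not be separable later. The downside is that the reported excess may be smaller. Counting from the operation also leaves untouched the separate question of post-operative days that precede the infection.
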